**Inclusion criteria**
•Age ≥ 18 years
•Ischemic stroke confirmed by head CT or MRI and vessel occlusion confirmed by CTA, MRA, or DSA
•Patients receiving endovascular treatment
•First ever stroke or pre-stroke mRS ≤ 2
•Signed informed consent by a patient or their legally authorized representative.

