### Intervention

Intravenous thrombolysis with alteplase, tenecteplase, or urokinase can be used before and/or during EVT according to local or national guidelines. Femoral artery or radial artery puncture with local anesthesia is used for EVT. The choice of the anesthetic strategy (conscious sedation or general anesthesia) will be determined by the anesthesiology team and the neurointerventionalist according to a case-by-case basis. EVT will be carried out according to the usual practice of each center, including EVT with stent retrievers, thromboaspiration, balloon angioplasty, stenting, or a combination of these approaches. Intra-arterial thrombolysis with alteplase, tenecteplase, or urokinase and antithrombotic treatment with tirofiban, aspirin, clopidogrel, cilostazol, or ticagrelor are permitted in this registry at the operator's discretion. Systolic blood pressure and diastolic blood pressure will be recorded. Digital subtraction angiography (DSA) and a cone beam CT (or non-contrast CT) will be performed after EVT to evaluate recanalization and exclude intracranial hemorrhage. The number of passes to achieve successful recanalization as well as the use of adjunctive antithrombotics, if pertinent, will be recorded. Recanalization is graded according to the modified thrombolysis in cerebral infarction (mTICI) score, and successful recanalization is defined as having an mTICI grade of 2b-3.

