### Outcomes

The primary outcome is the proportion of patients who achieve functional independence (modified Rankin Scale score, mRS ≤ 2) at 90 days. The minimum and maximum values of the modified Rankin Scale score are 0 and 6, respectively; a higher score means a worse outcome with 6 indicating death.

The secondary outcomes include the following: (1) the percentage of patients with excellent functional outcome, defined as an mRS score of 0 to 1 at 90 days, (2) distribution of mRS at 90 days, (3) changes in National Institutes of Health stroke scale (NIHSS) at 24 h, 48 h, and 12 days, (4) proportion of symptomatic intracranial hemorrhage (sICH) within 48 h, defined as an increase in 4 or more points on the NIHSS that is caused by intracranial hemorrhage (ECASS-III definition) (2), (5) proportion of death within 7 days, (6) procedural complications, including vessel dissection, contrast extravasation, embolization into a new territory, femoral access complications, and (7) discharge disposition.

Exploratory outcomes include the following: (1) the association between neuroimaging within 48 h and clinical outcome (neuroimaging includes brain CT, MRI, or DSA); (2) changes in serum biomarkers at 48 h, including matrix metalloproteinases, proinflammatory cytokines, brain-derived neurotrophic factor (BDNF), neurofilament light chain, serum complement C3, C-reactive protein, albumin, copeptin, D-dimer, and uric acid; (3) transcranial Doppler ultrasound data within 24 h, including blood velocity and pulsatility index, which will be collected at some centers; and (4) dynamic changes of cortical blood oxygen saturation by near-infrared spectroscopy within 24 h, which will be collected at some centers.

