### Sample size determination

According to a previous report (9), the proportion of functional independence at 90 days (mRS of 0–2) was 46% after EVT within 7 h of onset. After a two-sided test was performed with a power of 80% and an α set at 0.05, the calculated sample size is 1,565 cases. Considering a loss to follow-up rate of 25%, the sample size was therefore readjusted to 1,800 cases. Considering that patients with anterior circulation occlusion within 7 h of onset account for ~60% of the enrolled population, this registry has been designed to include 3,000 patients.

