### Statistical analysis

Statistical analyses will be performed based on all enrolled participants or their legally authorized representatives who signed and did not withdraw informed consent. All data will be analyzed with SPSS 23.0 Software. The mean ± standard deviation (SD) will be used if continuous data are normally distributed, and the median and interquartile range (IQR) will be used if continuous data are non-normally distributed. Categorical data are expressed as a number (percentage). Differences between the primary endpoint and secondary endpoints such as mRS (0–1) at 90 days, the proportion of symptomatic intracranial hemorrhage at 48 h, the proportion of intraparenchymal hemorrhage at 48 h, and the occurrence of all-cause mortality at 7 days will be compared using binary logistic regression. The analysis will be adjusted for confounders, including age, sex, baseline NIHSS, pre-stroke mRS, prior stroke, baseline ASPECTS, site of arterial occlusion, transfer of patient, time from last known well, and IVT use (for EVT patients). The 90-day mRS score will be compared using ordinal logistic regression. Change in the NIHSS score will be compared using a general linear model. Time to events of stroke recurrence and other vascular events will be compared using Cox regression. Statistical tests are considered significant when the two-sided *P*-value is < 0.05.

The outcomes in DETECT2-China will be further analyzed by the following subgroups: (1) onset of symptoms to recanalization time (<7 vs. ≥7 h), (2) age (<65 vs. ≥65), (3) NIHSS score on admission (6–16 vs. ≥17), (4) baseline ASPECTS (<6 vs. ≥6), (5) thrombectomy technique (stent retriever vs. contact aspiration or other techniques), (6) anterior circulation vs. posterior circulation, (7) mean systolic blood pressure during the intervention (≤ 120 vs. >120 mmHg), (8) mechanical thrombectomy alone vs. bridging thrombectomy, (9) mothership vs. drip and ship models, (10) stroke etiology (ICAD vs. cardioembolic vs. others), and (11) use of general anesthesia vs. conscious sedation.

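### The early/late subgroup is split on onset-to-recanalization time, a post-treatment time that patients without recanalization do not have

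*Protocol article*

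**What the plan says.** The Statistical analysis section lists eleven subgroups. The first is "onset of symptoms to recanalization time (<7 vs. ≥7 h". It is the only listed subgroup based on time.

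The article does not define a recanalization time. The nearest definition is in the Intervention section, which grades reperfusion after the procedure and states that "successful recanalization is defined as having an mTICI grade of 2b-3". A lower grade is therefore an anticipated result.

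Entry does not depend on that grade. Table 1 requires "Patients receiving endovascular treatment", and the Study population section obliges centers to enter consecutive treated patients. On the analysis set, the article says "Statistical analyses will be performed based on all enrolled participants", subject to consent given and not withdrawn.

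Two other time references appear. The adjusted models include "transfer of patient, time from last known well, and IVT use (for EVT patients", so time from last known well is a covariate. The Sample size determination section takes its reference rate from an earlier report in which functional independence "was 46% after EVT within 7 h of onset".

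**The concern.** Whether and when a vessel is reopened is a result of treatment. Using it to form an early and a late group raises three problems.

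- **Undefined for some patients.** Those who never reach recanalization have no value, and the article gives no rule for them. The rule could then be chosen after the data are seen.
- **Selection on success.** If these patients are left out or placed in ≥7 h, everyone in <7 h has been recanalized. The rate of mRS 0–2 in that stratum is too high as a description of early-treated patients, provided failures do worse.
- **Mixing of causes.** A long or difficult procedure can carry an early presenter past 7 h. A difference between strata then reflects procedural success and duration as well as how late treatment began.

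The Discussion names the extended time window among the controversies the registry should help to clarify, so readers are likely to look at this comparison.

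**Working it through.** The article gives no figure for this subgroup, for the share of failed procedures, or for outcome after failure, so there is no stated figure to reproduce. Everything below is illustration. The sample-size figures do not depend on this subgroup.

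**Inputs.** From the documents: 46% independence (Sample size determination), taken here as the all-patient rate, and 3,000 planned patients. Assumed: *f*, the share without recanalization, 5–20%; *p*, the rate of mRS 0–2 among them, 10–30%.

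**1. Failures dropped: effect on the pooled rate.** Rate among recanalized patients = (0.46 − *f* × *p*) / (1 − *f*).

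| *f* | *p* | Patients leaving (of 3,000) | Calculation | Rate | Shift, points |
|---|---|---|---|---|---|
| 5% | 30% | 150 | (0.46 − 0.015)/0.95 | 46.8% | +0.8 |
| 10% | 20% | 300 | (0.46 − 0.020)/0.90 | 48.9% | +2.9 |
| 15% | 20% | 450 | (0.46 − 0.030)/0.85 | 50.6% | +4.6 |
| 20% | 10% | 600 | (0.46 − 0.020)/0.80 | 55.0% | +9.0 |

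If failures did no worse (*p* = 46%), the shift would be 0. It is also 0 if every patient is kept on a clock that everyone has.

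**2. Failures dropped: effect on the early/late difference.** Assume 50% (early) and 40% (late) among recanalized patients and *p* = 20%. The difference with failures dropped is always 10 points. With failures kept in the stratum where they belong:

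- Failures 10% early, 10% late: 47% − 38% = 9 points, so dropping them adds 1 point.
- Failures 10% early, 20% late: 47% − 36% = 11 points, so dropping them removes 1 point.
- Failures 20% early, 10% late: 44% − 38% = 6 points, so dropping them adds 4 points.

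The direction is not fixed.

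**3. Failures coded ≥7 h: no true time effect.** Assume 46% in both groups, a 60/40 early/late split, *f* = 15% and *p* = 15%.

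- Rate among recanalized patients: (0.46 − 0.15 × 0.15)/0.85 = 51.5%.
- Early group, 1,800: 1,530 recanalized, 270 failures. Late group, 1,200: 1,020 recanalized, 180 failures.
- <7 h stratum: the 1,530 recanalized early patients, at 51.5%.
- ≥7 h stratum: 1,020 recanalized late patients plus all 450 failures. (1,020 × 0.5147 + 450 × 0.15)/1,470 = 592.5/1,470 = 40.3%.

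A difference of about 11 points appears although time has no effect. This calculation leaves out the further shift from long procedures that cross the 7 h mark.

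**The case against.** The strongest objection is that the article nowhere excludes patients without recanalization. Its analysis set is all enrolled participants, and a classification rule for one of eleven subgroups is normally left to an analysis plan. This stands in part. A reader might infer that failed procedures drop out, but the document does not say so. An end-of-procedure time could also be assigned to them. That would keep every patient, but it would be a different variable, still fixed after treatment and still driven by procedure length. The point is therefore about a variable that the article names with its cut-point and that suits the purpose badly, and not about missing detail.

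A reader might also infer that the study's result is biased upward. The documents do not support that. The primary outcome is an overall proportion that does not use this split, and the other ten subgroups do not use it either.

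A third tempting reading is that <7 h is demonstrably on a different clock from the population used for sizing. The Sample size determination section names no end-point for its 7 h window, so the two cannot be shown to differ. That population is also limited to the anterior circulation, and the article plans no test of this subgroup against 46%. What stands is that the clock is unstated there.

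Finally, other subgroups are procedural too (technique, blood pressure during the intervention, anesthesia), and in a single-arm registry time to recanalization is a legitimate descriptor. That is a reason to keep it as a description, but not as the registry's only early/late split.

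**Conclusion.** The point holds for this subgroup alone. Its defining time is set after treatment and does not exist for enrolled patients who are not recanalized. If they are dropped or coded ≥7 h, the <7 h stratum describes only successful procedures, and the contrast is not a clean comparison of earlier with later treatment.

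The size cannot be fixed from the documents. The increase in the pooled rate under dropping rests on the assumed failure share and on failures doing worse. The low end is negligible and the high end is not. If failures are dropped, bias in the contrast can go either way. If they are coded ≥7 h, the example shows that a sizeable difference in favor of <7 h can arise from classification alone. The change is worth making because it is cheap and removes a choice that could otherwise be made after seeing the data.

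**What to change.** - Define subgroup (1) for every treated patient as onset (or last known well) to arterial puncture, <7 vs ≥7 h. If puncture time is not captured, use onset (or last known well) to hospital arrival, which the Baseline characteristics section already lists.
- In Sample size determination, state the same clock for the population described as within 7 h of onset.
- Keep onset-to-recanalization time as a descriptive analysis restricted to patients with mTICI 2b-3, labeled as such.

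The cost is a few lines of wording. The small downside is that puncture time is not among the times listed under Baseline characteristics. An eCRF field or retrieval from procedure records may be needed, and with enrollment planned for January 2022 to December 2024 at 30 centers, part of that could be retrospective. The arrival-based version avoids this. No treatment or visit changes.

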### Study population

In the DETECT2-China prospective registry, eligible participants are LVO-AIS patients who received EVT. The detailed inclusion and exclusion criteria are shown in Table 1. To avoid selection bias, all participating centers are obliged to enter consecutive patients undergoing EVT in this study.

**Table 1 T1:** Inclusion and exclusion criteria.

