**Exclusion criteria**
•The presence of intracranial hemorrhage at the baseline neuroimaging
•Pre-stroke mRS ≥ 3
•Other serious illness that would confound the clinical outcome at 90 days
•Unavailable neuroimaging data
•Other unsuitable conditions judged by the investigator.

CT, computed tomography; MRI, magnetic resonance imaging; mRS, modified Rankin Scale.

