## Discussion

The DETECT2-China is a prospective, multi-center registry, aiming to evaluate the clinical outcomes and safety of EVT in Chinese LVO-AIS patients.

This trial has two distinct characteristics. First, this is a real-world registry in China. Differences in body mass, comorbidities, and etiology of AIS patients between different ethnicities are of interest to study as the five early LVO randomized clinical trials were performed in America, Europe, and Australia (4, 6–9). The subjects included in randomized clinical trials are more homogeneous in baseline characteristics, while the inclusion and exclusion criteria of DETECT2-China are not restrictive given the design of the real-world registry (13). Thus, DETECT2-China is expected to provide real-world data covering a comprehensive group of patients, and this could be helpful to understand some of the main controversies in EVT, for example, the benefit of EVT for AIS with large infarct core, very low or very high NIHSS due to LVO, medium-sized vessel occlusions, posterior circulation strokes, isolated cervical carotid occlusions, extreme ages, extended time window without advanced neuroimaging selection, etc. In addition, this registry will provide valuable data about different EVT modality treatment paradigms such as mothership vs. drip and ship. Second, this registry will enroll all patients who received EVT such as intra-arterial thrombolysis, stent retrievers, thromboaspiration, balloon angioplasty, stenting, or various combinations of these approaches. The design is consistent with clinical practice. Collectively, DETECT2-China should reveal comprehensive data about EVT for Chinese LVO-AIS patients in a real-world setting.

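### The NIHSS subgroup (6–16 vs. ≥17) is not exhaustive: enrolled patients scoring 0–5 fall in neither stratum

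*Protocol article*

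**What the plan says.** The list of subgroups in the Statistical analysis section has eleven entries. The third is "NIHSS score on admission (6–16 vs. ≥17". The same section states that "Statistical analyses will be performed based on all enrolled participants", subject to consent.

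Eligibility is set in Table 1. The inclusion criterion on treatment is simply "Patients receiving endovascular treatment". The only functional threshold concerns the state before the stroke: "First ever stroke or pre-stroke mRS ≤ 2", mirrored by an exclusion for a pre-stroke mRS of 3 or more. No inclusion or exclusion criterion mentions NIHSS. The exclusions end with a general clause, "Other unsuitable conditions judged by the investigator".

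The Study population section adds that "all participating centers are obliged to enter consecutive patients undergoing EVT in this study".

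The Discussion says that "the inclusion and exclusion criteria of DETECT2-China are not restrictive given the design of the real-world registry", and gives "very low or very high NIHSS due to LVO" as one example of the controversies that the data might help to clarify.

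**The concern.** A subgroup analysis of all enrolled patients should place each patient with a known value in exactly one stratum. This one starts at 6, although nothing in the eligibility rules keeps out patients with lower scores. Followed as written, the NIHSS strata do not add up to the enrolled population, and results by admission severity leave out the mildest strokes.

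The stake is modest but real. Results for this group would go unreported in the one analysis organised by admission severity. If a 0–5 stratum were added after the data had been seen, it would be post hoc, whereas adding it now makes it pre-specified.

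**Working it through.** No figure in the plan needs reproducing. The main check is one of coverage, followed by an illustration of size.

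**1. Who can be enrolled.** Table 1 has five inclusion and five exclusion criteria. Read in full, none sets a lower or upper limit on NIHSS. The investigator-discretion clause may remove individual patients but is not an NIHSS floor. With consecutive entry required, an otherwise eligible, consenting patient who scores 0–5 and receives endovascular treatment is to be entered.

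**2. What the strata cover.** The two categories, 6–16 and ≥17, cover every score from 6 upward without overlap. Scores 0, 1, 2, 3, 4 and 5 are in neither.

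**3. Comparison with the other numeric cuts in the list.**

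| Subgroup | Categories | Covers whole scale? |
|---|---|---|
| Onset to recanalization | <7 vs. ≥7 h | yes |
| Age | <65 vs. ≥65 | yes (adults) |
| Baseline ASPECTS | <6 vs. ≥6 | yes |
| Mean systolic pressure during the procedure | ≤120 vs. >120 mmHg | yes |
| Admission NIHSS | 6–16 vs. ≥17 | no, 0–5 missing |

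Only the NIHSS cut has a gap, and the article gives no reason for it.

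**4. Size.** Inputs:
- Planned enrolment of 3,000 and loss to follow-up of 25%, both from Sample size determination.
- Share with NIHSS 0–5: not given. Assumed range 5–10%.

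Patients in neither stratum:
- 0.05 × 3,000 = 150
- 0.10 × 3,000 = 300

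Patients with a 90-day mRS, if the 25% loss applies equally to this group:
- 150 × 0.75 = 112.5, taken as 112
- 300 × 0.75 = 225

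Half-width of a 95% interval for the proportion with mRS 0–2, using 1.96 × √(p(1 − p)/n) at the worst case p = 0.5:
- n = 112: 1.96 × √(0.25/112) = 0.093, or 9.3 points
- n = 225: 1.96 × √(0.25/225) = 0.065, or 6.5 points

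Without any loss to follow-up the same formula gives 8.0 points (n = 150) and 5.7 points (n = 300). Those values are too favourable, given the attrition that the plan itself expects.

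**The case against.** The strongest case against is that the gap matters little. It touches one of eleven subgroup analyses. Patients scoring 0–5 stay in the primary outcome, in the secondary outcomes and, where classifiable, in the other ten subgroup analyses. Baseline NIHSS is already an adjustment covariate. No primary estimate or sample-size figure changes. All of this stands and limits the weight of the point. It does not close the gap: an adjustment coefficient does not report how many patients in the lowest range reached independence, bled or died.

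A reader might infer that the plan contradicts its own Discussion by dropping the very patients it promises to inform. The documents do not support that. The Discussion says only that the data may help, by way of example. Other items in the same list, such as medium-sized vessel occlusion and isolated cervical carotid occlusion, have no dedicated subgroup either. The fault therefore rests on eligibility set against strata. The Discussion adds only that the omitted group is of interest to the authors.

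A reader might also infer that a 0–5 stratum would show whether treatment benefits these patients. It would not. The Limitations section acknowledges that there is no control group, so the stratum gives outcome rates in treated patients only.

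Finally, an analysis plan that is not shown might define the strata differently. But this is not a detail left open: the article states specific cut-points, and an analysis that follows them inherits the gap.

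**Conclusion.** The point holds as a minor, easily corrected fault. The NIHSS strata as printed do not cover the population that the eligibility criteria admit. The consequence is confined to this subgroup analysis.

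The coverage finding needs no numerical assumption. Its practical size does: the 5–10% share is an assumption, and so is applying the 25% loss evenly. On those terms about 150–300 enrolled patients would be left out, of whom about 112–225 would have a 90-day outcome. If few such patients are treated at the participating centers, the omitted group shrinks and its interval widens further, but the strata remain incomplete as soon as one is enrolled.

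The defect gives no ground for asking that NIHSS also be fitted as a continuous term. Baseline NIHSS is already in the adjustment set, and its functional form is ordinary analysis-plan detail.

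**What to change.** Restate subgroup (3), before the data are examined, as admission NIHSS 0–5 / 6–16 / ≥17. Report the 0–5 stratum descriptively, as numbers and proportions with confidence intervals, and state that without a control group it says nothing about the benefit of treatment.

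A lower category of ≤16 would also make the strata complete, but it would merge the very low scores with the moderate ones and hide the group that the Discussion mentions. If leaving out 0–5 is deliberate, one sentence giving the reason would serve, together with the number of patients omitted.

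The cost is one line of wording. No new data are needed, because NIHSS is already assessed at screening (Table 2). The drawback is a small third stratum with a wide interval, of the order shown above.

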**Clinical assessment**						
Diagnosis	x					
Head CT/MRI	x	x	x			
Cortical oxygen monitoring^a^		x				
TCD monitoring^b^		x				
NIHSS assessment	x	x	x	x	x	
mRS assessment	x					x
Medical history	x					
Demographic characteristics	x					
Vital signs	x	x	x	x	x	x
mTICI score	x					
TOAST classification					x	

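### The blood-pressure subgroup uses a value measured during treatment, and the named confounders omit anaesthetic strategy and admission blood pressure, on which it plausibly depends

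*Protocol article*

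**What the plan says.** The Statistical analysis section lists eleven subgroups. The seventh divides patients by "mean systolic blood pressure during the intervention" (≤120 vs >120 mmHg). The eleventh is "use of general anesthesia vs. conscious sedation".

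The same section names the adjustment variables: "The analysis will be adjusted for confounders, including age, sex, baseline NIHSS, pre-stroke mRS, prior stroke, baseline ASPECTS", followed by "site of arterial occlusion, transfer of patient, time from last known well, and IVT use (for EVT patients". That makes ten variables. Anaesthesia and blood pressure are not among them. The word that introduces the list leaves it open to additions.

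On anaesthesia, the Intervention section says: "The choice of the anesthetic strategy (conscious sedation or general anesthesia) will be determined by the anesthesiology team and the neurointerventionalist", case by case. It also says that systolic and diastolic pressure will be recorded, without giving the timing. Table 2 schedules vital signs at screening and at every later visit ("Vital signs x x x x x x"). The Limitations section acknowledges selection bias, non-standardised treatment and the absence of a control group.

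**The concern.** A subgroup variable is easiest to interpret when it is fixed before treatment. Mean pressure during the procedure is not: it can be shaped by the anaesthetic given and by the pressure with which the patient arrived. That dependence is clinical reasoning and is not stated in the document. The case-by-case choice of anaesthetic is stated, however, and means that the choice can follow the patient's condition.

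If general anaesthesia both lowers intra-procedural pressure and goes with a different prognosis, the group at or below 120 mmHg holds more general-anaesthesia patients than the other group. Part of any outcome difference then belongs to anaesthesia selection. The same argument applies to admission pressure. At stake is a result that could be read as an effect of blood pressure during the procedure when it is partly an artefact of who was treated how.

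**Working it through.** **Step 1: compare the text.** There is no stated figure to reproduce, so the first check sets the sections side by side.

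- Subgroup variable: measured during treatment (Statistical analysis, subgroup 7).
- Named covariates: six in the first part of the list and four in the second, ten in all. Anaesthetic strategy and admission pressure are absent.
- Availability: anaesthetic strategy must be recorded for subgroup 11. Admission pressure should be among the vital signs at screening in Table 2, although the table does not itemise them.
- Role of the adjustment: every patient receives EVT and there is no control group, so the planned regressions can mainly be contrasts between kinds of treated patient. On that reading the named list is the adjustment set for subgroup 7.

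**Step 2: illustrate the size.** All inputs except N are assumed. Suppose pressure has no effect on outcome. Let g be the proportion under general anaesthesia (0.3–0.5), a the proportion with mean SBP ≤120 under general anaesthesia (0.40–0.50), and b the same proportion otherwise (0.15–0.20). Independence is 40% under general anaesthesia and 50% otherwise.

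- P(GA | ≤120) = g·a / [g·a + (1−g)·b]
- P(GA | >120) = g(1−a) / [1 − g·a − (1−g)·b]
- False gap = 10 points × the difference between these two proportions

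| g | a | b | GA in ≤120 | GA in >120 | Gap (points) |
|---|---|---|---|---|---|
| 0.3 | 0.40 | 0.15 | 0.120/0.225 = 53% | 0.180/0.775 = 23% | 3.0 |
| 0.3 | 0.40 | 0.20 | 0.120/0.260 = 46% | 0.180/0.740 = 24% | 2.2 |
| 0.3 | 0.50 | 0.15 | 0.150/0.255 = 59% | 0.150/0.745 = 20% | 3.9 |
| 0.3 | 0.50 | 0.20 | 0.150/0.290 = 52% | 0.150/0.710 = 21% | 3.1 |
| 0.5 | 0.40 | 0.15 | 0.200/0.275 = 73% | 0.300/0.725 = 41% | 3.1 |
| 0.5 | 0.40 | 0.20 | 0.200/0.300 = 67% | 0.300/0.700 = 43% | 2.4 |
| 0.5 | 0.50 | 0.15 | 0.250/0.325 = 77% | 0.250/0.675 = 37% | 4.0 |
| 0.5 | 0.50 | 0.20 | 0.250/0.350 = 71% | 0.250/0.650 = 38% | 3.3 |

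General anaesthesia therefore makes up 46–77% of the lower-pressure group and 20–43% of the higher, with a crude gap of 2.2 to 4.0 points. Values of g between the ends change little: g = 0.4 with a = 0.50, b = 0.15 gives 0.200/0.290 − 0.200/0.710 = 0.408, or 4.1 points.

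**Step 3: compare with sampling error.** Take N = 3,000 with complete follow-up.

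- Smallest gap: groups of 780 and 2,220, overall independence 47%. SE = √[0.47 × 0.53 × (1/780 + 1/2,220)] = 2.1 points, so the bias is about 1 standard error.
- Largest gap in the table: groups of 975 and 2,025, overall independence 45%. SE = √[0.45 × 0.55 × (1/975 + 1/2,025)] = 1.9 points, so the bias is about 2 standard errors.

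**Step 4: widen the assumptions.** Set independence under sedation to 46%, the rate the article cites in its sample-size section. Let general anaesthesia be used in 30% or 50%, with SBP ≤120 in 30–60% under general anaesthesia against 15–20% otherwise. Let the anaesthesia–outcome odds ratio run from 0.6 to 1.25. The pressure odds ratio without adjustment for anaesthesia then runs from 0.78 to 1.11 when the truth is 1.00. The false rejection rate at a nominal 5% runs from about 5% to about 89%. When the anaesthesia–outcome odds ratio is 1.0 there is no bias.

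Steps 2 to 4 all give crude figures. None takes account of the ten covariates the plan does name.

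**The case against.** Several objections have force. The covariate list is open-ended, so it is accurate to say that neither variable is named, not that neither will be adjusted for. Separate covariate sets for each of eleven subgroups are ordinarily left to an analysis plan. The named covariates (NIHSS, ASPECTS, occlusion site, transfer, time from last known well) would remove part of any bias that arises from sicker patients being given general anaesthesia. No input to the illustration except the sample size and the 46% comes from the document. This is one subgroup in a registry that openly states its selection bias and lack of a control group.

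These points limit the size and certainty of the problem. They do not remove it. The article does publish a list and a cut-point for this contrast. It treats anaesthesia as important enough for its own subgroup, yet does not name it where it plausibly matters as a confounder. A general admission of selection bias does not deal with confounding by variables already in the database.

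A reader might go further and infer that subgroup 11 is also faulty: that it leaves out patients treated under local anaesthesia, counts conversions from sedation as general anaesthesia, and is confounded for those reasons. The document does not support this. It mentions local anaesthesia only for access ("Femoral artery or radial artery puncture with local anesthesia is used for EVT") and then defines exactly two strategies, which are the two levels of subgroup 11. It never mentions conversion, and how converted patients are classified is detail that an article may leave to the full protocol. Such matters would in any case be problems of classification, not of confounding.

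**Conclusion.** The point holds for subgroup 7 and is modest. The contrast rests on a value measured during treatment, and the named confounders leave out two variables on which it plausibly depends and which should already be collected. The vulnerability follows from the text together with ordinary clinical reasoning. The size does not. A crude false gap of about 2.2 to 4.0 points is an illustration under stated assumptions; it would be smaller after the listed adjustments and zero if anaesthesia is unrelated to outcome once those are made. The contribution of admission pressure was not quantified, and its direction is not established. The primary estimate, the overall proportion independent at 90 days, is unaffected, and no fault in subgroup 11 is established.

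**What to change.** For the subgroup 7 models, add anaesthetic strategy and admission systolic pressure to the named covariates. State that the result will be presented as an association and not as an effect of blood pressure.

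Do not make the mirror-image change to subgroup 11. Intra-procedural pressure lies downstream of anaesthesia, so adjusting for it there would remove part of whatever difference anaesthesia makes.

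The cost is a sentence or two of analysis wording. Both variables should already be in the database; it should be confirmed that the screening vital signs include blood pressure. Two extra covariates cost negligible precision with a planned 3,000 patients.
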